#### Statistical methods

For the primary and secondary outcomes we will estimate odds ratios with 95% confidence intervals. We will calculate the rates of self-reported contraception use per ward and willingness to use the WC. Descriptive analyses will be conducted, and several regression models will be run to determine the impact of IPC on each outcome variable of interest. All regression models will control for baseline characteristics of relevance to the outcome (either as potential confounders or as explanatory factors). Backward elimination methods will be used to remove non-statistically significant factors that do not improve the fit of the model and do not confound other associations observed. Multilevel models may be implemented to control for individual and ward level correlation, as individuals are nested within wards.

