**Methods/design:**

A baseline survey of 2314 randomly selected 18- to 24-year-old sexually active men and women has been conducted. The WC and mass media will be introduced throughout 40 urban wards in and surrounding Lusaka, Zambia. The baseline survey will serve as a quasi-control arm to determine the impact of introducing the WC with mass media. Half of the wards will be randomly allocated to additionally receive the IPC intervention. A single-blind randomized controlled trial will determine the impact of the IPC intervention on knowledge, uptake, and use of the WC. After one year, another 2314 individuals will be randomly selected to participate in the endline survey.

We hypothesize that (1) the distribution and media campaign of the WC will increase overall condom use in selected urban wards, and specifically use of the WC; (2) the IPC intervention will significantly impact knowledge, acceptability, and use of the WC.

The primary outcome measures are use of the WC, use of any condom, and willingness to use the WC. Secondary outcomes include measures of knowledge, acceptability, and choice of contraception.

Odds ratios will be estimated to measure the effect of the intervention on the outcomes with 95% confidence intervals. All analyses will be based on the intention-to-treat principle.

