**Fig. 1 Fig1:**
[figure not shown]
Summary of conceptual framework

The primary objectives of this evaluation are:To assess the effect of the introduction of the WC on the overall condom market (self-reported condom use and self-reported use of WC)To determine the additional effect of an IPC intervention on self-reported *use of the WC* as compared with just mass media including a website (controlling for any differences between the intervention and control groups)To determine the additional effect of an IPC intervention on self-reported *use of any condom* as compared with just mass media including a website (controlling for any differences between the intervention and control groups)To determine the additional effect of an IPC intervention on *willingness to use an FC* (and specifically, the WC) as compared with just mass media including a website (controlling for any differences between the intervention and control groups)

The secondary objectives of this evaluation are:5.To determine the effect of an IPC intervention on self-reported *knowledge, attitudes, and practices regarding the FC, specifically the WC*, as compared with just mass media including a website (controlling for any differences between the intervention and control groups)6.To determine the effect of an IPC intervention on community-level *acceptability of an FC, specifically the WC*, compared with just mass media including a website (controlling for any differences between the intervention and control groups)7.To determine the effect of an IPC intervention on self-reported *changes in interpersonal communication with sexual partners* regarding contraceptive use as compared with just mass media including a website (controlling for any differences between the intervention and control groups)8.To assess women’s and men’s preferences for condom brands.

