A structured questionnaire was administered to each eligible and consented individual who met the inclusion criteria. Survey interviewers were either male or female and work for Innovations for Poverty Action (IPA) Zambia. Each interview lasted about one hour and took place in the home but away from other household members, in private. The questionnaire collects socio-demographic information, information regarding condom use, sexual behavior, knowledge and beliefs specifically regarding condoms, contraceptive options, and communication with sexual partners. A small reimbursement amount was provided to participants who completed the survey. The study enrolled both men and women.

After the baseline survey was completed in January 2016, all 40 wards were randomized to receive the control (WC plus mass media) or intervention (WC plus mass media plus IPC), and were allocated by an IPA statistician using a Stata program. Ward level population density based on the 2010 census data, ward level poverty, and average distance to the nearest health facility were used to stratify the randomization. Additional balance checks were conducted to ensure randomization was successful. Each ward has been mapped including the IPC sites, and all visited houses enumerated and given an ID. Since randomization, the IPC intervention has been implemented in intervention wards only. Only the IPA statistician and the implementing partner (the SFH) know the allocation of wards. The endline survey is planned for March 2017, and will follow the same protocol as outlined above for the baseline survey. The endline survey will have additional questions regarding exposure to the mass media and IPC intervention, including pictures to prompt recall. Households will be randomly selected for both surveys; the same households will not be approached.

The Consolidated Standards of Reporting Trials (CONSORT) randomization and survey structure are described in Fig. 3.

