### Data management and analysis plan

The data are collected into an Android phone using SurveyCTO software; the data obtained are cleaned and exported into Stata for analysis. A high frequency check is run every two to three days to highlight any errors in data collection. Twenty percent of all participants (eligible or ineligible) are being randomly selected for back checking. The back check includes confirmation of ineligibility or administration of a 5- to 10-min version of the original survey to compare responses. All data are encrypted using Boxcryptor and stored on the SurveyCTO cloud and Box. A de-identified version of the data and statistical code will be shared on Dataverse at the completion of the study.

We will report the trial according to the CONSORT standards for reporting RCTs. This is a behavioral intervention unlikely to produce adverse effects, so analysis will be undertaken immediately once the endline survey has been completed. Baseline survey data will be analyzed to measure differences between the groups and between the wards at baseline. Randomization can be checked at this point. The main analysis will take place after endline data have been collected, to measure the impact of the introduction of the WC and the IPC intervention on condom use, controlling for any potential confounders or explanatory factors detected from the baseline analysis.

To assess the impact of the introduction of the new and premium WC on the Zambian condom market, the evaluation team will use the baseline survey as a quasi-control arm. While there are limitations with this approach, it will allow for measurement of changes in condom use, brand switching, user preferences, and uptake of the new product. The main limitation is that the study cannot determine attribution; however, given the challenges to create a better counterfactual, the evaluating and implementing teams agreed that this is the best approach in view of programmatic constraints.

The baseline survey will occurred at a time when there was no WC product available, no mass media, and no IPC. The study outcomes are self-reported condom (male or female) use ever, during the past 6 months, and at last sexual intercourse. The study will measure these indicators at baseline (no WC available) and endline (WC available). By analyzing changes in these indicators, the study will show changes in overall condom use as well as uptake of the WC in areas with only mass media versus mass media and IPC.

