For the RCT component of the study, we will analyze the impact of the IPC intervention on our outcomes of interest (male condom use, WC use, willingness to use the WC), comparing intervention to control wards. Analyses will be conducted in Stata v12 (StataCorp, College Station, TX, USA). Results will be adjusted for any ward level clustering if it is identified. Multivariate regression analyses will be carried out to determine the impact of the IPC intervention on condom use (male condom and WC), controlling for demographic characteristics of participants.

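### The IPC effect models prune covariates by backward elimination under differing rules, and nothing excludes endline covariates that IPC itself can change

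*Protocol article*

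**What the plan says.** The protocol article describes covariate adjustment in four places.

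- **Objectives and hypothesis:** the IPC objectives are each to be estimated "controlling for any differences between the intervention and control groups".
- **Data management and analysis plan, main analysis:** "Baseline survey data will be analyzed to measure differences between the groups and between the wards at baseline". The effects are then estimated "controlling for any potential confounders or explanatory factors detected from the baseline analysis".
- **Data management and analysis plan, RCT component:** the multivariate models are run "controlling for demographic characteristics of participants".
- **Statistical methods:** "All regression models will control for baseline characteristics of relevance to the outcome (either as potential confounders or as explanatory factors". Next comes the pruning rule: "Backward elimination methods will be used to remove non-statistically significant factors that do not improve the fit of the model". That sentence goes on to keep factors that confound other observed associations.

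On the sample, the abstract says: "After one year, another 2314 individuals will be randomly selected to participate in the endline survey". Survey and randomization adds: "Households will be randomly selected for both surveys; the same households will not be approached".

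**The concern.** Two things look wrong.

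First, the models are to use baseline characteristics, but nobody in the endline sample has an individual baseline record. Any individual covariate in the endline models is collected after IPC has been running. The questionnaire covers condom knowledge and beliefs and communication with partners. IPC is meant to change these, and knowledge, attitudes and partner communication reappear as secondary outcomes. They also predict condom use, so a rule that keeps whatever improves fit would tend to retain them. Conditioning on them strips the mediated part from the randomised effect. If something unmeasured drives both knowledge and use, the adjusted contrast also loses the protection of randomisation.

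Second, the adjustment set depends on the data: on arm differences that randomisation produced by chance, and on significance in the fitted model. The 95% confidence intervals carry no stated allowance for that step. Because the four statements differ, two analysts could each follow the protocol and report different IPC effects on the same primary outcome.

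**Working it through.** The plan gives no figure on this point to reproduce. The check sets the passages side by side and then uses two illustrations with assumed inputs.

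**1. Timing.** The baseline survey was completed in January 2016 and the wards were randomised afterwards (Survey and randomization). The product launch was set for February 2016 (abstract). The endline survey is dated January 2017 (Trial status) or March 2017 (Setting and participants), which is 11 to 13 months after launch. With new households at endline, individual covariates are about a year post-intervention. Age and sex are unaffected by that. Knowledge, beliefs, partner communication and IPC exposure are not.

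**2. Pre-IPC data that do exist.** Ward population density, poverty and distance to a health facility were used to stratify the randomisation. The baseline survey also has about 58 interviews in each of the 40 wards. Baseline characteristics are therefore missing at the individual level only.

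**3. The four rules.** They call for adjustment for any arm difference, for factors detected at baseline, for participants' demographics, and for relevant characteristics after elimination. These are different sets. Only the demographic rule comes close to excluding variables that IPC can change.

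**4. What mediator adjustment would do (assumed inputs).** Let knowledge be 40% in control wards and 50% to 70% in IPC wards. Let condom use be 40% without knowledge, and let knowledge have an odds ratio of 1.5 to 3 for use. IPC has no direct effect.

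- Weakest case (50%, odds ratio 1.5): use with knowledge is 50%. Control use is 0.6 × 0.40 + 0.4 × 0.50 = 0.44. IPC use is 0.5 × 0.40 + 0.5 × 0.50 = 0.45. The total odds ratio is (0.45/0.55)/(0.44/0.56) = 1.04.
- Strongest case (70%, odds ratio 3): use with knowledge is 66.7%. Control use is 0.6 × 0.40 + 0.4 × 0.667 = 0.507. IPC use is 0.3 × 0.40 + 0.7 × 0.667 = 0.587. The total odds ratio is (0.587/0.413)/(0.507/0.493) = 1.38.

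Adjusted for knowledge, the IPC odds ratio is 1.00 in both cases. With a direct odds ratio of 1.2 added, the total is 1.25 to 1.64 and the adjusted value is 1.20. On the percentage-point scale, a 3-point effect with mediated share s becomes 3 × (1 − s), or 2.25, 1.5 and 0.75 for s = 0.25, 0.5 and 0.75. That only restates the assumed s.

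**5. What automatic elimination does to type I error (null simulations, nominal 5%).**

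- *Ward-level regression, 40 observations, 6000 runs per setting, elimination at p > 0.05.* With 5, 10 and 15 irrelevant candidates, type I error was 6.0%, 7.1% and 8.3%. With weakly prognostic ones it was 7.3%, 10.7% and 13.9%. Unadjusted and full fixed models gave 4.8% to 5.5%. This is not the plan's model.
- *Individual-level data, 40 wards × 58, cluster-robust tests.* The ICC is an assumption taken from the design effect of 2 in the Sample size section: 1 + 57 × ICC = 2, so ICC = 1/57 = 0.0175. With 10 to 15 candidates and 3000 runs, elimination gave 5.2% to 6.9%, the full fixed set 5.7% to 6.8%, and no adjustment 4.5% to 5.3%. Elimination itself added at most about 0.4 points.
- *A second individual-level run, 1000 runs per setting.* Elimination gave 5.4% to 7.2% in four settings, against 5.4% to 7.9% for the full fixed set. With ten ward-level candidates the figures were 12.9% and 12.1%.

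The simulation error near 5% is √(0.05 × 0.95/1000) = 0.7 points with 1000 runs and 0.4 points with 3000. At the individual level the excess follows the number of ward-level terms more than the elimination step.

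**The case against.** The strongest reply is that no passage names knowledge, attitudes or communication as a covariate. The covariates are described as baseline characteristics, and the passage on the RCT comparison itself speaks of demographics. The sentence can be carried out sensibly with age, sex and ward-level baseline data. The exact covariate list is commonly left to an analysis plan, which is not shown. All of this stands. A reader might infer that the trial will adjust for its own mediators, or that its baseline covariates cannot exist. The text supports neither: the first is a risk left open, and the second holds only for individual records.

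It is also fair that choosing prognostic factors from the baseline survey uses different people, before any endline outcome exists. That step does not depend on endline outcomes and need not be abandoned. Selecting on chance arm differences is another matter.

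A reader might further infer that elimination invalidates the 95% intervals. The individual-level simulations do not show that for automatic elimination, although they do not cover deliberate choice among models.

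What the reply does not remove is that the article positively commits to backward elimination for the randomised effect, and gives differing rules. An analysis plan that followed it would inherit both.

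**Conclusion.** The point holds as a badly fixed analysis rule. The protocol article prunes the IPC models by significance, fit and observed confounding. It admits explanatory factors without excluding variables that IPC can change, in a sample whose individual covariates all postdate IPC, and it states the covariate rule in four differing ways.

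The size of any mediator bias cannot be derived from the documents. The odds ratios above rest on assumed knowledge levels and associations. The bias runs toward no effect only where mediated and total effects share a sign, which is the expected case here. The distortion from automatic elimination alone is probably modest: within about 1.5 points of type I error against the same covariates kept fixed, assuming an ICC of 0.0175 and cluster-robust tests. The firmer reasons for change are that the primary estimate should not depend on the data through covariate choice, and that it should keep the whole randomised effect.

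**What to change.** For the IPC comparison, replace backward elimination and adjustment for observed arm differences with one short covariate set, the same for all primary outcomes:

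- age and sex;
- the three ward-level stratification variables;
- the ward's baseline prevalence of the outcome, where it exists. It cannot exist for WC use, because the product was not available at baseline.

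Allow other prognostic factors found in the baseline survey only if they are fixed before endline data are seen and IPC cannot change them. State that endline knowledge, attitude, communication and IPC-exposure variables stay out of the effect models. Label any other model exploratory, and align the objectives, the analysis plan section and the statistical methods section with this single rule.

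The cost is a few sentences and no data, since the endline survey was still being planned at submission. Data-driven trimming is lost, along with a few ward-level degrees of freedom. With each ward variable as a single term, 40 wards less intercept, arm and four ward terms leaves 34. The ten-candidate simulation shows why the ward-level list must stay short.

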### Ethics

Individuals who meet the study inclusion criteria will give written informed consent. The interviewer will inform the participant that a study is being conducted on contraception, specifically knowledge and use of FCs, in order to improve SRH outcomes for this community, and that their time is very much appreciated and valued. The participant will receive an information sheet with additional details regarding the study in which they are enrolling. After this step, the participant will receive and sign for the small compensation (30 kwacha of talk time), and the questionnaire can be administered. Interviewers will conduct the survey in a private area to protect anonymity and reduce the likelihood that responses are influenced by external household factors.

The questionnaires will be assigned an anonymous ID number, and de-identified. They will be stored safely and not accessed by anyone except the evaluation team (principal investigators, co-investigators, and analysts), for confidentiality. All personal identifying information (PII) will be removed from the dataset. This study has received approval from both IPA’s and Zambia’s institutional review boards, IRB (IRB No. 10854) and Excellence in Research Ethics and Science (ERES) Converge (IRB No. 00005948). Any modifications to the protocol or survey will be submitted to both IRBs for review but are not anticipated. We have also received Zambia’s Ministry of Health’s approval to implement the study. The informed consent form and information sheet are provided in Additional file 2.

## Discussion

Results from the trial will provide rigorous evidence on the impact of introducing the new WC product on overall condom use and effective strategies to increase knowledge, acceptability, and uptake. This trial will contribute towards the evidence base on social marketing of condoms and community-based IPC interventions to increase uptake. The focus on young adults in urban areas and their knowledge and use of contraceptives has not been well studied. This trial is aimed at understanding the introduction of a novel contraceptive product to urban youths, and is unique in a number of ways.

First, this is the only RCT of the newly designed and marketed WC in urban sub-Saharan Africa. No studies have evaluated the impact of introducing a premium FC product (the WC) in a market where male condoms and the FC2 have been available. Further, an impact evaluation of social marketing comprised of mass media and an IPC intervention to increase condom use among a general population of young adults has never been conducted, although smaller studies between 1990 and 2010 suggest that social marketing can increase condom use [8]. One recent cluster RCT measured the impact of a Facebook page on the use of condoms for STI prevention and found a positive effect, but noted that it diminished over time [8]. Studies suggest that, despite their widespread availability and low cost, male condoms are not used as often or as consistently as they should be; therefore, adding the WC to the market could increase the levels of protected sex overall [9]. Studies suggest that when both types of condoms are available, consistent users will alternate male and female condoms as complements, not replacements for each other [9]. The WC may also be used more by long-term couples, whereas male condom use decreases significantly once relationships are defined [10]. The WC may serve as an alternative for women who are not able to negotiate male condom use [10].

Second, this is the first RCT of a community-based IPC intervention led by paid, trained IPC agents and targeting the general youth population. Some recent studies have highlighted aspects of IPC that can make it more successful, such as inclusion of stories and dialogue, demonstrations, role playing, games, and negotiation skills. IPC interventions that are dialogue-based are well suited for promoting openness and discussion about sensitive or stigmatizing topics such as condom use among couples and peer networks. Social networks can be used to diffuse information about condoms and reinforce condom use norms through IPC, increasing acceptability [11]. Previous programs or interventions with messages highlighting the positive benefits of the FC (e.g., increased sexual pleasure and autonomy) may also increase uptake [3]. IPC interventions that include demonstrations can be critical in improving women’s comfort level with FCs and shift attitudes towards the FC [12]. Women report that the overall acceptability of the FC improves over time with practice [13–15]. A US trial found the strongest predictors of FC use were having had instruction and skills training, and intending to use the method [16]. Knowing how to use an FC and feeling comfortable with insertion is critical, and initial findings suggest that demonstration is a necessary component for a successful rollout.

No single trial or initiative will answer the question of how the WC specifically will impact the condom market, and whether uptake will increase with mass marketing and IPC intervention. This trial will provide evidence on effectiveness of IPC interventions for increasing knowledge, acceptability, and uptake of the WC and condoms, generally. The generalizability of these findings may depend on the marketing of the WC and the culture in other regions of Zambia or in a different region. For example, the promotion of the FC as a woman-controlled method backfired in some countries because male partners viewed FCs as threatening to their control over their partner’s sexual behavior [17, 18].

Recommendations on the impact of IPC approaches for increasing condom uptake and other SRH services will be developed based on the results of this trial. Findings will be written into a report for PSI and WomanCare Global, and a paper will be submitted for publication to a peer-reviewed journal. The evaluation team will work closely with the SFH and PSI to organize a dissemination event subsequent to the completion of the study to share results with local and global stakeholders (government officials, non-governmental organizations (NGOs), international NGOs (INGOs), donors) working on SRH research, programs, and policies in Zambia and at the global level.

